## Objectives {7}

The main purpose of this study is to compare the effects of two distinct treatment protocols (conventional shoulder musculoskeletal rehabilitation combined with aerobic exercises versus solely conventional shoulder musculoskeletal rehabilitation) on shoulder function, range of motion (ROM), pain, strength, kinematics, and supraspinatus tendon thickness in patients with type 2 DM after 12 weeks of intervention, and a subsequent followup at the week 20 (8 weeks after the end of the protocol). As a secondary objective, we will evaluate the association between AGE accumulation and shoulder pain, function, strength, kinematics, and supraspinatus tendon thickness in individuals with type 2 DM.

The hypothesis is that the addition of aerobic exercises to the shoulder-specific rehabilitation protocol will promote a greater decrease in shoulder pain and increase in functionality, range of motion, strength, and an adequate shoulder kinematics after 12 weeks, and a follow-up at week 20. Furthermore, regarding the association, the hypothesis is that a higher AGE accumulation is associated with higher shoulder pain, dysfunction, tendon thickness, shoulder kinematic disorders, and lower muscle strength in patients with type 2 DM.

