### Outcomes {12}

The results will be evaluated at 3 points: (1) baseline (before starting the intervention program), (2) after 12 weeks of intervention (after 48 h to 1 week from the last intervention), and (3) at the week 20 (follow-up). Regarding the outcomes, the shoulder assessed by the SPADI (Shoulder Pain and Disability Index) questionnaire will be considered as primary outcome; the secondary outcome will be shoulder pain, measured with NPRS scales. Other outcomes will include range of motion, measured using a digital inclinometer; isometric shoulder muscle strength, measured using a manual muscle dynamometer; shoulder kinematics, measured using three-dimensional inertial units measurement; supraspinatus tendon thickness, measured using an ultrasound; AGE accumulation, using a skin autofluorescence measurement; and HbA1c (hemoglobin a1c), fasting glucose and lipid profile measured by a simple blood test.

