### Participant timeline {13}

#### Sample size {14}

Sample size calculation was performed through the GPower software (version 3.1). The calculation was based on the study by Schmitt et al. [20], using the main outcome (SPADI questionnaire) to detect a mean difference of 16.8 points, considering a power of 80% and an Alfa of 5%. The sample size suggested was 16 per group; however, to account for possible withdrawals that may occur in this type of study, it will be increased by 20%, thus totaling 40 participants (20 per group).

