## Statistical methods

### Statistical methods for primary and secondary outcomes {20a}

Data will be analyzed using SPSS, version 20.0 (SPSS Inc. 233 S. Wacker Drive, Illinois USA). The statistical assumptions for all the tests will be assessed. In case of normality, to verify the effectiveness of protocols over time (12 weeks and follow-up of at week 20), a mixed model analysis of variance (ANOVA) with Bonferroni adjustment will be performed for pairwise comparisons. Variables that do not meet the ANOVA assumptions will be analyzed by the Mann-Whitney and Wilcoxon tests with Bonferroni correction a priori.

To assess the secondary objective of the study, Pearson’s or Spearman coefficient correlation, when applicable, and a linear regression analysis will be performed to assess the association between AGE accumulation and outcome measures.

The significance level will be set at 5% for all statistical analyses. Furthermore, the effect size will be calculated using the Cohen coefficient *d*.

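### An assumption check decides whether SPADI is analysed by mixed ANOVA or by Mann-Whitney and Wilcoxon tests, and the fallback does not fix a baseline-adjusted between-arm SPADI contrast

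*Protocol article*

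**What the plan says.** The section Statistical methods for primary and secondary outcomes {20a} begins with a check: "The statistical assumptions for all the tests will be assessed". Where normality holds, "a mixed model analysis of variance (ANOVA) with Bonferroni adjustment will be performed for pairwise comparisons". Where it does not, "Variables that do not meet the ANOVA assumptions will be analyzed by the Mann-Whitney and Wilcoxon tests with Bonferroni correction a priori". The rule applies variable by variable.

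Outcomes {12} names SPADI as the one primary outcome ("questionnaire will be considered as primary outcome; the secondary outcome will be shoulder pain, measured with NPRS scales"), with assessments at baseline, 12 weeks and week 20. Nothing in {20a} takes SPADI out of the switching rule.

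Objectives {7} asks a between-arm question about change: adding aerobic exercise "will promote a greater decrease in shoulder pain and increase in functionality". Sample size {14} is set on the SPADI points scale, "to detect a mean difference of 16.8 points, considering a power of 80% and an Alfa of 5" per cent.

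**The concern.** The hypothesis is about a difference between arms in how much SPADI changes. A mixed ANOVA with arm and three visits contains that contrast, although {20a} does not name the group-by-time term. The fallback splits the question into separate tests:

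- Wilcoxon looks at change inside one arm and cannot compare arms.
- Mann-Whitney compares arms, but the article does not say whether it ranks follow-up scores or change from baseline, or at which visit it decides the comparison.
- Baseline SPADI is not used as a covariate in either test.
- Neither test estimates a difference in SPADI points, so the result cannot be set directly against 16.8.

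The question answered for the primary outcome can therefore depend on an assumption check in about 16 to 20 people per arm. Both arms receive active rehabilitation, so both should improve. A pair of within-arm p-values, one below the threshold and one above, would then be easy to mistake for superiority.

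**Working it through.** **Inputs from the article.** Difference 16.8 SPADI points, power 80%, alpha 5%, 16 per group before and 20 after the withdrawal allowance (Sample size {14}); 1:1 allocation (Sequence generation {16a}); SPADI range 0 to 100 (Shoulder function measurement). The SD and the sidedness are not stated.

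**The plan's own figure.** For a two-sided t-test, 16 per group at 80% power needs d = 1.024, so SD = 16.8/1.024 = 16.4. The SDs that round up to 16 per group run from about 15.9 to 16.4, or about 18.1 to 18.7 if one-sided. The allowance reproduces: 16 × 1.2 = 19.2, rounded up to 20, and 16/0.8 = 20. The 16 cannot be confirmed without the SD, so SD 16.4 is an assumption from here on.

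**How often the switch could happen.** The check is not named. If it were a 5% normality test on each of six arm-by-visit cells, perfectly normal data would fail somewhere in about 1 − 0.95^6 = 26% of trials.

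**Power at a 16.8-point effect.** Simulation, 16 per arm, 2,000 runs per setting, unadjusted two-sided 5%. The baseline-to-follow-up correlation r and the distribution shapes are assumptions. The t-test on change stands in for the ANOVA's group-by-time contrast from baseline to week 12.

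| Data | r | Mann-Whitney, follow-up | Mann-Whitney, change | t-test, change | ANCOVA |
|---|---|---|---|---|---|
| Normal | 0.3 | 0.77 | 0.63 | 0.66 | 0.82 |
| Normal | 0.5 | 0.78 | 0.76 | 0.79 | 0.90 |
| Normal | 0.7 | 0.76 | 0.94 | 0.96 | 0.98 |
| Right-skewed | 0.3 | 0.91 | 0.77 | 0.68 | 0.83 |
| Right-skewed | 0.5 | 0.89 | 0.88 | 0.80 | 0.87 |
| Right-skewed | 0.7 | 0.88 | 0.98 | 0.95 | 0.95 |

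Repeat runs at r = 0.5 gave Mann-Whitney 0.76-0.79 against ANCOVA 0.89 in normal data. With scores floored at 0 they gave 0.74-0.76 against 0.87. Under heavier flooring, Mann-Whitney on change fell to about 0.66 while ANCOVA held 0.86-0.87.

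**Where the gap comes from.** At r = 0.5 the variance of change is 2(1 − r)SD² = SD², and the ANCOVA residual variance is (1 − r²)SD² = 0.75 SD². ANCOVA therefore works with d = 1.024/√0.75 = 1.18 instead of 1.02. Of the normal-data gap 0.89 − 0.76 = 0.13, about 0.89 − 0.79 = 0.10 is ANCOVA against the change contrast, and about 0.79 − 0.76 = 0.03 is the rank test.

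**Validity of Mann-Whitney.** With no treatment effect and a common 10-point improvement, it rejected in 3.5% to 5.4% of trials.

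**Wilcoxon read arm by arm.** If both arms improve equally and each within-arm test has power p, exactly one is significant with probability 2p(1 − p), which peaks at 0.50 when p = 0.5. With three visit pairs and an assumed level of 0.05/3, at r = 0.5:

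| Common improvement | Points (× 16.4) | One arm only |
|---|---|---|
| 0.4 SD | 6.6 | about 27% |
| 0.6 SD | 9.8 | about 48-49% |
| 0.8 SD | 13.1 | about 45% |
| 1.0 SD | 16.4 | about 24% |
| 1.2 SD | 19.7 | about 7% |

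At an unadjusted 5% with a 10-point common improvement, the range across r and shape was 27% to 49%.

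**The case against.** A reader might infer that the fallback replaces the treatment comparison with within-arm tests, or that it no longer tests whether the combined programme does better. The article does not support that. It names Mann-Whitney as well as Wilcoxon. Mann-Whitney compares the arms, and in a randomised trial it is a valid test at close to its nominal level. The Wilcoxon tests are added to it. Pairwise comparisons after the ANOVA would ordinarily include within-arm contrasts too, and nothing in the article says superiority will be read from them.

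Three further points stand:

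- Ranking raw scores is only one reading. Mann-Whitney on change would keep some of the baseline information and of the group-by-time question.
- The fallback applies when assumptions fail, so normal data are not its natural test bed. In the right-skewed simulations at r = 0.5 the power loss vanishes, and at r = 0.3 ranking follow-up scores beats ANCOVA.
- ANCOVA is not the planned analysis, so most of the normal-data gap at r = 0.5 is not caused by the switch.

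The article also commits to Cohen's d, so a mean-based effect size may be reported beside the rank test. It would then describe a different quantity from the one tested.

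An analysis plan that is not shown may name the score and the visit. It would not undo the switching rule, which the article states outright and applies to the primary outcome.

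**Conclusion.** The point holds in a limited form. A check on the trial data chooses the SPADI test. The fallback does not fix the score or visit, uses no baseline adjustment, gives no difference in points to compare with 16.8, and adds Wilcoxon tests that do not compare arms. This should be changed, but it does not invalidate the trial.

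The cost in power depends on the data. Against baseline-adjusted ANCOVA at r = 0.5 it is roughly 10 to 13 percentage points in normal or floored data, and nothing material in right-skewed data. The main objection is therefore that the question and the estimate change with the check; lost power comes second. The one-arm-only rate of about 24-49% measures how misleading arm-by-arm reading would be. It is not a false-positive rate of the plan, and it falls to about 7% at a common improvement of 1.2 SD.

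All simulated figures rest on an SD back-solved from 16 per group and on assumed correlations and distribution shapes. The Wilcoxon table also assumes a 0.05/3 level.

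**What to change.** In {20a}, prespecify one between-arm SPADI contrast, adjusted for baseline SPADI, at a named visit (for example week 12), and report it in SPADI points with a confidence interval. Use it whatever the normality check shows. If residuals are skewed, take the interval and p-value from a bootstrap, robust-variance or permutation version of the same model. Keep Mann-Whitney as a sensitivity analysis, with the score and visit named. State that within-arm Wilcoxon tests are descriptive and support no efficacy conclusion.

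Baseline SPADI is already collected, so no new data, visits or participants are needed. The cost is a change of wording and slightly more analysis work.

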### Interim analyses {21b}

Not applicable. Interim analyses will not be performed in the present study.

### Methods for additional analyses (e.g., subgroup analyses) {20b}

Not applicable. Additional analyses are not planned in the present study.

### Methods in analysis to handle protocol non-adherence and any statistical methods to handle missing data {20c}

The study will include only participants who attended at least 80% of the sessions and performed all the assessments (per-protocol). Furthermore, missing data will be handled by intention-to-treat analysis using the multiple imputation method.

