### Intervention description {11a}

Participants who meet the inclusion criteria for this study will initially be evaluated for demographic data including age, sex, weight, height, occupation, and time since type 2 DM diagnosis. The order of assessment of the main outcomes will be randomized. After participants complete the outcomes assessment, they will be randomly assigned to one of the two treatment groups: (1) shoulder-specific rehabilitation protocol group (SRG); or (2) shoulder-specific rehabilitation protocol plus aerobic exercise group (SAG). The randomization sequence will be performed through a computerized algorithm in GraphPad.

All measurements will be performed on the symptomatic side for shoulder pain. In the case of bilateral pain, the side with greater severity will be considered in the study as proposed in previous studies [16]. However, treatment will be carried out bilaterally. Outcomes measures will be performed always by the same evaluator.

Both treatment protocols will last 12 weeks, and they will be performed twice a week. All individuals will be evaluated before starting the treatment protocol (baseline), at the end of treatment (post 12 weeks), and at week 20 (8-week follow-up after the intervention) (Fig. 1). To minimize bias, the evaluator responsible to measure the main outcomes will be blinded to the type of treatment being performed. Before, during, and after each session, blood pressure, heart rate, and rating of perceived exertion will be measured.

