#### SRG: shoulder-specific rehabilitation group

The SRG protocol will be performed on groups with a maximum of 5 participants. Exercise intensity and difficulty will progress after completing 4 weeks of treatment, by increasing range of motion and loads (dumbbells) or resistance (elastic bands) in the exercises that are convenient. Each session will consist of 6 exercises: (1) pendulum exercise (10 repetitions—maintenance for 20 s); (2) slide in flexion of the arms on the table (2 sets of 10 repetitions, maintenance in maximum range for 20 s); (3) abduction and adduction mobility (2 sets of 10 repetitions, maintenance for 20 s) and full can abduction exercise; (4) wall slide—sliding of the arms on the wall (2 series of 10 repetitions, maintenance of 20 s); (5) internal and external rotation mobility (2 sets of 10 repetitions, maintenance for 20 s) and external rotators strengthening; (6) stretching of the posterior capsule (cross-body) and stretching of pectoralis minor (3 repetitions of 30 s, each). Pain will be evaluated during the protocol using the NPRS scale. The exercises proposed in this protocol are those already demonstrated to improve function, strength, range of motion, and pain in musculoskeletal disorders of the shoulder complex for general population [17, 18].

Each session of this protocol will last between 30 and 35 min. All sessions will be supervised by a physiotherapist with experience in physical exercise.

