### Criteria for discontinuing or modifying allocated interventions {11b}

Participants will be informed that exercises and rehabilitation interventions, other than those that will be received during the duration of the study, will not be allowed. Participants with less than 80% treatment attendance will be excluded from the study. Furthermore, data such as blood pressure, heart rate, saturation, and rating of perceived exertion will be measured before, after, and during the rehabilitation sessions. Capillary blood glucose will be evaluated at the beginning and at the end of each session. If the patient presents signs or symptoms of decompensation such as glycemia> 200 mg/dl or <80 mg/dl, systolic blood pressure > 180 mmHg, or diastolic blood pressure > 100 mmHg at rest, the session or evaluation will be immediately suspended, and the necessary measures will be taken.

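### Items 11b and 20c remove randomised participants for low attendance or missed assessments yet claim intention-to-treat, and no primary analysis set is named

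*Protocol article*

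**What the plan says.** Item 20c of the protocol article (non-adherence and missing data) gives two rules in consecutive sentences. The first is "The study will include only participants who attended at least 80% of the sessions and performed all the assessments (per-protocol". The second is "Furthermore, missing data will be handled by intention-to-treat analysis using the multiple imputation method".

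Item 11b (discontinuing or modifying interventions) adds "Participants with less than 80% treatment attendance will be excluded from the study".

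On timing, item 11a says "After participants complete the outcomes assessment, they will be randomly assigned to one of the two treatment groups", so attendance and completeness of follow-up are both known only after allocation. Item 20a plans a mixed-model ANOVA for the outcomes over time but names no analysis set. Item 20b says that no additional analyses are planned.

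**The concern.** A set limited to people with every assessment leaves no missed assessment to impute. A set that drops randomised people for poor attendance is not intention-to-treat. Item 20c invokes both without saying which result carries the superiority claim, so that choice could be made after the data are seen.

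The restriction also acts after randomisation. For the control arm (SRG) the plan says "Each session of this protocol will last between 30 and 35 min", while the combined arm (SAG) may need up to about 90 min per visit. If the longer visits cost SAG more attenders, and attendance is related to shoulder outcome, the people left in the two arms are no longer comparable. In addition, exclusion from the study, as opposed to exclusion from one analysis, may mean that the week 12 and week 20 SPADI of low attenders is not collected. An analysis plan written later cannot restore outcomes that were never measured.

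**Working it through.** **1. Attendance threshold.** Item 11a: "Both treatment protocols will last 12 weeks, and they will be performed twice a week". That is 12 × 2 = 24 sessions, and 0.80 × 24 = 19.2. A participant needs at least 20 sessions, and a fifth missed session leads to exclusion.

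**2. The rules side by side.**

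| Rule | Who is analysed | Missed assessments to impute |
|---|---|---|
| Item 20c, first sentence | at least 20 of 24 sessions and all assessments | none, by definition |
| Item 11b | at least 20 of 24 sessions | possible |
| Item 20c, second sentence | all 40 randomised, if intention-to-treat has its usual meaning | yes |

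**3. The plan's own sample size.** Item 14 starts from 16 per group and says "it will be increased by 20%, thus totaling 40 participants (20 per group". This reproduces: 16 / (1 − 0.20) = 20, and 16 × 1.2 = 19.2, rounded up to 20. The 16 itself cannot be checked because no SD is given. Solving backwards for a 16.8-point difference, 80% power and 5% alpha, a two-sided t-test needs a standardised difference of 1.02-1.06, so an SD of 15.9-16.4. The two-sided normal approximation gives 17.0, and a one-sided t-test 18.1-18.7. I use 16.4.

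**4. Possible bias when there is no true effect.** Assume that a latent attendance propensity has correlation r with SPADI outcome, that low attenders do worse, and that the lowest fraction p in each arm is excluded. The mean propensity of those kept is m(p) = φ(z_p)/(1 − p):

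- m(0.10) = 0.195
- m(0.30) = 0.497
- m(0.40) = 0.644

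The bias is b = r × SD × [m(p in SAG) − m(p in SRG)].

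**5. Type I error.** SE = 16.4 × √(1/n_SAG + 1/n_SRG). With 10% of 20 excluded, SRG keeps 18. With 30% or 40% excluded, SAG keeps 14 or 12. The SE is 5.84 for 14 v 18 and 6.11 for 12 v 18. The normal approximation is P(Z > 1.96 − b/SE) + P(Z < −1.96 − b/SE).

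| Excluded, SRG v SAG | r | Bias (points) | Type I error, approximation | Type I error, simulation |
|---|---|---|---|---|
| 10% v 30% | 0.3 | 1.48 | 5.7% | 5.7% |
| 10% v 30% | 0.5 | 2.47 | 7.1% | 6.8% |
| 10% v 40% | 0.3 | 2.21 | 6.5% | not run |
| 10% v 40% | 0.5 | 3.68 | 9.2% | 9.1% |
| 20% v 20% | 0.3 | 0 | 5.0% | 5.0% |

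At r = 0.2 the bias for the two unequal cases falls to 1.0 and 1.5 points. Bias scales with the SD. At 15.9 the smallest tabled non-zero value becomes 0.302 × 0.3 × 15.9 = 1.4, and at 18.7 the largest becomes 0.449 × 0.5 × 18.7 = 4.2. The approximate type I error does not change with the SD, because b and SE scale together.

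**6. Precision.** With SD 16.4, a two-sided t-test and equal arms, power for 16.8 points is 88% with 20 per group, 80% with 16, 74% with 14 and 67% with 12.

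**The case against.** The best defence is that item 20c answers a two-part heading: a per-protocol analysis for non-adherence and an intention-to-treat analysis for missing data. On that reading both can be run, and a statistical analysis plan that is not shown may name the primary one. This has weight. A reader might infer that the two rules can never both be followed, and the text does not support that. But the defence is incomplete. Item 20c restricts the study and not one analysis, item 11b does the same, item 20b plans nothing additional, and no sentence ranks the two sets.

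Second, a reader might infer that low attenders' week 12 and week 20 scores are definitely lost. No sentence says that assessments stop, and everyone randomised has a baseline SPADI, so imputation over all 40 stays feasible, though weaker. The supportable statement is that these scores may not be collected.

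Third, bias is neither certain nor of known direction. Unequal attendance is plausible from session length but is a prediction. If people who recover stop coming, the sign reverses and SAG looks worse.

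Fourth, a reader might argue that session suspensions for glycaemia make the rule select on glycaemic control. The protocol does not say whether a suspended session counts as attended, the limits apply to both arms, and the stated hypothesis concerns shoulder outcomes. The point does not rest on this.

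Finally, the 20% allowance for withdrawals may already be meant to include low attenders, so it is not shown that the analysed set must fall below 16 per group. The allowance protects precision, however, and not comparability between arms.

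**Conclusion.** The point holds in this form: the plan sets a post-randomisation exclusion beside an intention-to-treat claim, names no primary set, and words the exclusion so that outcomes may go uncollected. This rests on the text alone and needs no assumption. It should be corrected before analysis, because the conclusion of a superiority trial depends on it.

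The size is illustrative only. Under the assumed exclusion rates (10% v 30-40%), correlations (0.3-0.5) and back-solved SD (16.4), the spurious difference is about 1.5-3.7 points, or 9-22% of the 16.8-point target (1.48/16.8 and 3.68/16.8), with type I error of about 6-9%. With equal exclusion and the same selection mechanism in both arms it is zero, with type I error of 5%. The documents give none of the exclusion rates or correlations, so they support the statement that the rule can bias the comparison, not that it will.

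**What to change.** - In item 20c, define the primary analysis as all randomised participants in their allocated arm, whatever their attendance.
- In item 11b, replace exclusion from the study with wording that keeps low attenders in the week 12 and week 20 assessments unless they withdraw consent.
- Handle missing SPADI in that primary set by multiple imputation or a likelihood-based mixed model, and state which.
- Keep the set with at least 80% attendance only as a labelled per-protocol sensitivity analysis.

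The cost is a rewording of two items, notification of the ethics committee, and assessment visits that the schedule already contains. Even in the illustration, 2 SRG participants plus 6-8 SAG participants would be retained, so at most 8-10 people with two visits each. With fewer low attenders it is only a few visits. No increase in sample size is needed. The downside is that the primary estimate is diluted by non-adherence. The per-protocol sensitivity analysis shows the result among adherent participants.

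### If SPADI switches to rank tests, the multiply imputed intention-to-treat analysis has no poolable between-arm estimate; one pre-named repeated-measures model would remove the problem

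*Protocol article*

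**What the plan says.** **Missing data.** Section 20c states that "missing data will be handled by intention-to-treat analysis using the multiple imputation method". The sentence before it sets a different population: "The study will include only participants who attended at least 80% of the sessions and performed all the assessments (per-protocol"). Section 11b adds: "Participants with less than 80% treatment attendance will be excluded from the study".

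**Tests.** For normally distributed outcomes section 20a plans that "a mixed model analysis of variance (ANOVA) with Bonferroni adjustment will be performed for pairwise comparisons". Otherwise: "Variables that do not meet the ANOVA assumptions will be analyzed by the Mann-Whitney and Wilcoxon tests with Bonferroni correction a priori". It says that the assumptions of all tests will be checked, and makes no exception for SPADI, the primary outcome. For the secondary objective, "a linear regression analysis will be performed to assess the association between AGE accumulation and outcome measures".

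**Design.** Section 12 says "The results will be evaluated at 3 points": baseline, week 12 and week 20. Section 14 gives 16 per group, raised by 20% for withdrawals to 20 per group, 40 in total.

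**The concern.** Multiple imputation produces several completed data sets, and its purpose is one combined estimate with one standard error. That requires the same analysis in every completed set, and an analysis that yields an estimate and a variance. Section 20a guarantees neither for SPADI. If the assumption check fails, the planned analysis becomes rank tests, for which the plan names no effect estimate. If the check is run in each completed set, it may pass in some and fail in others, and an ANOVA result cannot be combined with a rank-test result.

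At stake is the trial's main number: the between-arm SPADI difference in everyone randomised, with its confidence interval. With 20 per arm and a questionnaire bounded at 0 and 100, a failed check is a realistic possibility. How often it would fail cannot be worked out from the documents.

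**Working it through.** **1. How much imputation to expect.** The withdrawal step reproduces: 16 / 0.8 = 20, and 16 × 1.2 = 19.2, rounded up to 20; 2 × 20 = 40. A 20% loss is 0.2 × 40 = 8 participants, leaving 32. The 16 per group can be neither confirmed nor refuted, because no SD is given. With a difference of 16.8, 80% power and two-sided 5%, a t test needs 16 per group if the SD is about 15.9 to 16.4. The point here does not depend on that figure.

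**2. What pooling needs.** With m imputed sets, estimates Q_k and variances U_k, Rubin's rules give the mean of the Q_k as the estimate and T = mean(U_k) + (1 + 1/m)B as its variance, where B is the variance of the Q_k between sets.

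| Planned analysis (section 20a) | What each imputed set supplies | Can it be pooled? |
|---|---|---|
| Pairwise comparison | 1-df mean difference and its SE | Yes, by Rubin's rules |
| Group-by-time F | (2 − 1)(3 − 1) = 2 numerator df | Yes, by a multi-parameter rule |
| AGE regression (secondary objective) | Coefficient and its SE | Yes, but it is not the arm comparison |
| Mann-Whitney | p-value for arms at one visit | No planned estimate and variance |
| Wilcoxon | p-value for visits within one arm | No, and it does not compare arms |

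**3. Behaviour in one assumed scenario.** The simulation assumed 20 per arm, SD 16.4, correlation 0.5 between baseline and each later visit and 0.6 between the later visits, and about 20% lost after baseline depending on baseline score. It used 20 imputations. These are assumptions, not protocol figures. The first four rows used 1,000 runs each and the last used 4,000.

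| Analysis | Type I error | Power at 16.8 points |
|---|---|---|
| Week-12 difference, imputed, Rubin's rules, no baseline adjustment | 2.8% | 81% |
| Group-by-time F, imputed, multi-parameter (D2) rule | 3.9% | 83% |
| Mann-Whitney, imputed, ad hoc median p-value | 6.4% | 85% |
| Week-12 t test on observed data, no baseline adjustment | 4.2% | 82% |
| Week-12 model on observed data, arm + baseline | 4.9% | 88% |

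Monte Carlo error at 1,000 runs is √(0.05 × 0.95 / 1000) = 0.7 points for type I error and √(0.81 × 0.19 / 1000) = 1.2 points for power.

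**4. Reading the table.** Both ANOVA-branch quantities pool without inflation. The median p-value is a workaround that the plan does not contain; its 6.4% is (6.4 − 5.0) / 0.7 = 2 Monte Carlo errors above nominal, and it still gives no SPADI difference. The gain from 81% to 88% comes largely from baseline adjustment: the unadjusted t test on observed data has 82%. It is not evidence against multiple imputation.

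**The case against.** The strongest reply is that the plan already contains what is needed. The pairwise comparisons are mean differences with standard errors, F tests have a pooling rule, and the choice of rule is detail that an article may leave to the analysis plan, which is not shown. All of this stands for the ANOVA branch, and an unstated pooling rule is not itself a fault. What remains is the combination of two stated choices, imputation and the rank-test switch.

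Three stronger readings are tempting, and the documents support none of them:

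- A reader might infer that the intention-to-treat analysis is impossible, or that section 20a offers nothing that can be pooled. The first three rows of the first table show otherwise.
- A reader might infer inflated type I error from reporting one imputed set or averaging the sets. No section plans either shortcut.
- A reader might infer that the completers' result will become the headline. Section 20c names both populations and does not say which is primary.

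Two further replies carry weight. The term mixed model ANOVA may already mean a linear mixed model, in which case the parametric branch is close to the proposal. And imputation and a likelihood model can rest on the same missing-at-random assumption, so preferring the latter here is a matter of simplicity, not validity.

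**Conclusion.** The point holds for one branch of the plan. If SPADI fails the assumption check, or fails it in only some imputed sets, no single intention-to-treat estimate of the between-arm difference follows from what is written. If the check passes throughout, the result can be pooled.

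The size is modest. The problem arises only with missing SPADI data and a failed check together, and neither frequency is known beyond the 20% withdrawal allowance. The simulated figures rest on a single week-12 scenario with assumed SD, correlations and loss. They show that the proposed approach behaves acceptably (4.9% type I error), not that the planned imputation fails. The change is worth making because it affects the primary result and costs little.

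**What to change.** 1. In section 20a, name one primary SPADI analysis: a linear mixed model for repeated measures on all randomised participants' observed data, with arm, visit, arm-by-visit and baseline SPADI, and small-sample degrees of freedom. Report the between-arm difference with its 95% CI. If mixed model ANOVA already means a linear mixed model, say so and add baseline SPADI.
2. Remove the rank-test switch for SPADI.
3. In section 20c, keep multiple imputation as a sensitivity analysis that pools the same contrast by Rubin's rules.
4. Reconcile sections 11b and 20c. They restrict the study to people with at least 80% attendance and all assessments done, which leaves nothing to impute, yet announce intention-to-treat. The model is intention-to-treat only if SPADI is still collected and analysed for participants below 80% attendance.

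**Cost.** Items 1 to 3 change analysis wording only and use SPADI data already scheduled. Item 4 may mean extra follow-up assessments. The downside is that a normal-theory model is used even if residuals are skewed; a bootstrap interval for the same contrast would check this. A participant with no SPADI score after baseline adds nothing to the estimated difference in this model, so retention still matters.
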